## Abstract

The gastrointestinal (GI) tract of a fetus in utero is sterile but it becomes colonized with environmental microorganisms shortly after birth. Since the gut microbiota undergoes substantial changes in early life, healthy gut microflora is essential to an infant's gut health and immune system and probably also has an effect on overall health status in later life. Probiotics, defined as viable microbial preparations that have a beneficial effect on the health of the host, represent a rapidly expanding field. Although randomized controlled trials using probiotics in infants have shown promising results in the prevention and treatment of common diseases such as diarrhea and allergy, little is known about whether probiotics could offer benefits to healthy infants. We have designed a randomized controlled trial to test the hypothesis that an oral preparation of probiotics is superior to placebo in improving digestive and immune function in healthy infants.

The trial will be a randomized, double-blind, placebo-controlled, 2-parallel-group study in Shanghai, China. After a 2-week run-in period, 200 exclusively formula-fed healthy infants aged 4 to 6 months will be randomly allocated to receive either a probiotic product containing *Bifidobacterium infantis* R0033, *Bifidobacterium bifidum* R0071, and Lactobacillus helveticus R0052 or an identical placebo once daily for 4 weeks and will be followed up for 8 weeks. The duration of the subject's participation will be 14 weeks, with a total of 5 visits: inclusion (Visit 1, Day 1), start of intervention (V2, D15), end of intervention (V3, D44), and follow-up (V4 and V5, D72 and D100). Stool and saliva samples will be collected at the first 3 visits to measure microbial populations and secretory immunoglobulin A (SIgA), respectively. Physical examination will be performed at each visit, and tolerance records will be completed 1 day prior to each visit. The primary endpoints will be the changes in the composition of fecal microbiota, particularly the *Bifidobacterium bifidum* population. The secondary endpoints will include the change in salivary SIgA level, growth parameters, digestive tolerance, and adverse events.

An effective, practical, and acceptable probiotic intervention in manipulating the gut microbiota and boosting the immune system in formula-fed infants would represent a major clinical advance. The administration of probiotic supplementation or follow-on formula to infant may be associated with some clinic benefits.

## Introduction

1

The gastrointestinal (GI) tract of a normal fetus in utero is generally thought to be sterile. Newborn infants exit the uterus and enter an extrauterine environment filled with microbes. During the birth process and rapidly thereafter, microbes from the mother and the surrounding environment colonize the GI tract of the infant.^[1]^ However, the intestinal microbiota of the infant undergoes substantial development in early life. From an initial low diversity and low complexity, the intestinal microbiota slowly develop and mature, reaching an adult state around 3 years of age.^[2]^ Therefore, the first 2 to 3 years of life are the most critical period in which one can intervene to shape the microbiota as best as possible. Gut-associated immune tissue represents almost 80% of the immune system,^[3]^ making the composition of intestinal microbiota an important factor in the immune system. It is considered that the onset of many diseases possibly relates to disruption of the early colonization and establishment of the gut.^[4]^ All these factors indicate that healthy gut microflora is essential to infant's gut health and immune system and probably also has an effect on overall health status in later life.

Probiotics, defined as viable microbial preparations that have a beneficial effect on the health of the host, represent a rapidly expanding field. The demand for probiotics in clinical applications and as functional foods has been dramatically increasing in spite of limited understanding of their mechanisms. Numerous randomized controlled trials using probiotics in infants have shown promising results in the prevention and treatment of common diseases such as diarrhea and allergy.^[5–8]^ Among the possible mechanisms of probiotic intervention is promotion of a nonimmunologic gut defense barrier, which includes the normalization of increased intestinal permeability and altered gut microecology. Another possible mechanism of probiotic intervention is improvement of the intestine's immunologic barrier, particularly through local immunoglobulin A (IgA) responses and alleviation of intestinal inflammatory responses, which produce a gut-stabilizing effect.^[9]^ However, little is known about whether probiotics could offer benefits to healthy infants.

Among a number of bacterial species of that are found in the GI tract, *Bifidobacterium* and *Lactobacillus* species have been explored extensively in human and animal studies. The 2 species are recognized to have health-promoting properties and are added to commercial foods such as infant formula and used in pharmaceutical probiotics to enhance the protective gut microbiota, thus improving intestinal microbial balance.^[10]^*Bifidobacterium infantis* releases bioactive factors and prevents TNF-α- and IFN-γ-induced drops in transepithelial resistance to protect intestinal epithelial cell barrier function.^[11,12]^*Bifidobacterium bifidum* increases local IgA levels in the intestine and prevents diarrhea and shedding of rotavirus.^[13,14]^*Lactobacillus helveticus* inhibits *Campylobacter jejuni* invasion of intestinal epithelial cells.^[15]^ Its surface-layer protein can exert anti-inflammatory effects by reducing the activation of NF-κB on intestinal epithelial cells.^[16]^

However, the interpretation of clinical trials is difficult to compare due to the differences in endpoints, and variations in the probiotics used, as well as their doses and strains. It is well known that substantial differences exist between different probiotic bacterial species and strains. A recent review has suggested that sufficient evidence is available to warrant further evaluation.^[17]^ Huang et al^[18]^ examined the effect of a probiotic mixture containing *Bifidobacterium infantis*, *Bifidobacterium bifidum*, and *Lactobacillus helveticus* on the intestinal flora in rodent animal models and found that the numbers of bifidobacteria were higher in the probiotic group than those in the control group. Cazzola et al^[19]^ investigated the efficacy of a synbiotic supplementation including the above 3 strains in reducing common winter diseases in children and observed that the supplementation could decrease the risk of occurrence of common infectious diseases.

Therefore, we hypothesize that a combination of the above 3 strains containing *Bifidobacterium infantis*, *Bifidobacterium bifidum*, and *Lactobacillus helveticus* might be beneficially effective on infants’ overall health. Here, we have provided a protocol for a randomized controlled trial to determine the effects of a combination of the novel 3-strain probiotics on digestibility and immunity in healthy infants.

## Materials and methods

2

### Statistical analysis

2.1

Statistical analysis of all data will be performed by a specialized statistician in a blind manner. To estimate the efficacy of this trial, both the intention-to-treat and per-protocol populations will be analyzed. Baseline characteristics will be compared by unpaired Student's *t*-test (parametric test) or Mann–Whitney test (nonparametric test) and chi-square or Fisher's exact test (if one of the expected frequency < 5). All statistical analyses of the data will be performed using SAS software version 9.3 or higher (SAS Institute Inc., Cary, NC), and a *P*-value < 0.05 will be considered statistically significant. The target variables for analysis are as follows.

### Primary analysis

2.2

The primary endpoints, the V2-V3 changes in *Bifidobacterium bifidum*, *Bifidobacterium longum ssp. infantis*, *Lactobacillus helveticus*, *Clostridium perfringens*, *Enterococcus*, *Enterobacteria*, and *Bacteroides* in stools will be analyzed using the following ANCOVA model (SAS PROC MIXED):

*Y* = Product +Baseline + (Product × Baseline)

where

Y = V2–V3 change in fecal microbiota

Product = study products

Baseline = baseline value (V2)

Product × Baseline = Product − Baseline interaction

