### Secondary analysis

2.3

The above-mentioned ANCOVA model will be conducted for analysis of the V2–V3 change in salivary SIgA levels.

A within-group analysis to compare V2 and V3 values (e.g., fecal microbiota and salivary SIgA) will be conducted in each product group using a paired Student's *t*-test or a Wilcoxon signed-rank test, depending on the condition of application of the statistical test.

The outcomes related to GI symptoms and well-being (weekly average number of stools, stool form, amount of stools, color of stools, number of crying incidents, and duration of crying) will be analyzed using the following ANOVA model for repeated measurements (subject will be considered as a random effect, using SAS PROC MIXED):

Y = Product + Week + (Product × Week)

where Y = study endpoint at Wr (D8 to D15), W1 (D16 to D22), W2 (D23 to D29), W3 (D30 to D36), or W4 (D37 to D43)

Product = study products

Week = W1 to W4 weeks (between V2 and V3 visits)

Product × Week = interaction between the product and the week

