### Safety analysis

2.5

All AEs will be listed, and descriptive statistics (imputability and intensity) of all the registered AEs will be provided by product. Infant growth endpoints (e.g., weight, height, and head circumference) will be analyzed using the same ANCOVA model used to analyze the primary endpoint. The proportion of subjects showing at least 1 AE will be compared between groups using a chi-Square or Fisher's exact test. The number of events will be compared between groups using a Poisson regression.

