### Stool collection and bacteriological examination

3.8

Fresh stool samples will be collected in plastic bags, maintained anaerobically, and then sent to the lab for analysis. Stool samples (0.5 g) will be then mixed in 5 mL of sterile Ringer's solution containing 5% cysteine, allowed to vortex for 5 to 10 minutes, and shifted the supernatant for geometric dilution in a reagent bottle in sterile conditions.

Various media will be used for the selective isolation of different microorganisms: freshly prepared Man, Ragosa, and Sharpe (MRS) agar to which Mupirocin lithium salt is added, for *Bifidobacteria*; LBS agar supplemented with 1 mL/1000 mL of Tween 80 and 1.3 mL/1000 mL of glacial acetic acid, for *Lactobacilli*; TSC agar to which 0.8 mL/100 mL of 5% D-cycloserine is added, for *Clostridium perfringens*; modified GAM agar, to which 80 μg/mL of vancomycin, 1 μg/mL of kanamycin, 0.01 mL/100 mL of 1% vitamin K1, 0.25 g/100 mL of hemin, and 7 mL/100 mL of blood are added, for *Bacteroides*; bile esculin azide (BEA) agar, for *Enterococci*; and violet red bile dextrose (VRBD) agar, for *Enterobacteria*.

The seeded, streaked culture plates will be placed in anaerobic containers to maintain anaerobic conditions and then will be incubated at 37°C. Each anaerobic container contains a resazurin oxygen reduction indicator to ensure *anaerobicity* during incubation. The MRS, LBS, and modified GAM plates will be incubated anaerobically for 48 hours; the BEA, TSC, and VRBD agar plates will be incubated anaerobically for 24 hours. Colony counts will be done manually and expressed as CFU/g; numbers over 300 will be designated as too numerous to count (TNTC).

After incubation, colonies with representative morphology and color typical of specific species will be randomly selected and identified with the microorganism MASS system for confirmation.

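### The common ANCOVA contains Product × Baseline with an uncentred baseline and names no contrast; read through its Product term, it compares the arms at a baseline of zero

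*Protocol article*

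**What the plan says.** Section 2.2 (Primary analysis) states that the V2 to V3 changes in seven fecal organisms or groups "will be analyzed using the following ANCOVA model (SAS PROC MIXED)". The model's right-hand side is "Product +Baseline + (Product × Baseline)". The covariate is defined as "Baseline = baseline value (V2)", that is, the measured value itself. No centring is mentioned. Nothing says whether the result is the Product test, a difference in least-squares means, or the interaction.

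The same model is used twice more:
- Section 2.3 (Secondary analysis): "The above-mentioned ANCOVA model will be conducted for analysis of the V2–V3 change in salivary SIgA levels".
- Section 2.5 (Safety analysis): weight, height and head circumference "will be analyzed using the same ANCOVA model used to analyze the primary endpoint".

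Two other passages bear on the size of the problem. Section 3.8 gives the scale of the bacterial data, "Colony counts will be done manually and expressed as CFU/g", with no log transformation stated. Section 3.2 says that no formal sample size calculation was done, so there is no planned effect, SD or power.

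**The concern.** The abstract states the hypothesis as superiority of the probiotic over placebo, which calls for the average difference in change between the arms. In a model with separate baseline slopes per arm, that difference is not a single number: it varies with baseline. With an uncentred covariate, the Product coefficient and the default Type 3 Product test in PROC MIXED refer to the difference where baseline equals zero.

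Two things are at stake. First, the target changes: if the slopes differ, the effect at zero can differ from the average effect in size and even in sign. Second, even with equal slopes, the estimate at zero is an extrapolation when zero lies far from the data, and its standard error grows accordingly. The model serves the primary, immune and growth endpoints alike, so one ambiguous line affects most of the trial's between-arm comparisons.

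**Working it through.** **Inputs from the protocol article.** Model and covariate definition (2.2); reuse for SIgA and growth (2.3, 2.5); 100 infants per arm (3.2); 1:1 allocation (3.1); significance level 0.05 (2.1), taken here as two-sided. The article gives no power, effect size or baseline mean or SD, so there is no figure of its own to reproduce.

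**Reference case (assumption).** Take the effect for which a test of the average difference has 80% power with 100 per arm:

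d = √(2/100) × (1.960 + 0.842) = 0.396 residual SD.

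**Standard error at baseline zero.** With the interaction in the model, each arm has its own line. The variance of a fitted arm value at zero is σ²[1/n + m²/((n−1)s²)], where m and s are the baseline mean and SD. For the difference between arms:

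Var = (2σ²/n) × [1 + (n/(n−1)) × (m/s)²].

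The bracket is the variance inflation relative to the average-effect test. Call it k². Power is then Φ(2.80/k − 1.96) + Φ(−2.80/k − 1.96).

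| Baseline mean/SD | k² | Power of Product test |
|---|---|---|
| 0 | 1.0 | 80% |
| 0.5 | 1.25 | 71% |
| 1 | 2.0 | 51% |
| 1.5 | 3.3 | 34% |
| 2 | 5.0 | 24% |
| 4 | 17 | 10% |
| 8 | 66 | 6% |

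Half of the 80% is gone at a ratio of about 1.3. With 50 per arm, and the effect reset to give 80%, the figures are practically the same.

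**Simulation check** (5,000 trials per ratio, 100 per arm, equal true slopes). The uncentred Product test rejected in 78, 69, 51, 24, 10 and 7% of trials at ratios 0, 0.5, 1, 2, 4 and 8. The model with centred baseline and interaction, and the model without interaction, both stayed at 78 to 81% throughout and agreed with each other to about 0.1 point.

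**Where the endpoints might fall** (all baseline figures below are assumptions):
- *Log10 counts, organism found in every infant*, mean 7, SD 1: ratio 7, power 7%.
- *Log10 counts, undetected scored as 0, detected values as above*: 50% undetected gives ratio 0.98 and power 51%; 90% undetected gives ratio 0.33 and power 76%.
- *Raw CFU/g, lognormal*, with log10 SD of 0.3, 0.5 or 1.0: ratios 1.28, 0.60 and 0.07, power about 40%, 67% and 80%.
- *Weight*, mean 7.5 kg: with SD 0.6 kg the ratio is 12.5, k is about 12.6 and power about 6%; with a generous SD of 1.5 kg the ratio is 5 and power about 8 to 9%. Section 3.3 limits weight at inclusion to the range from the 20th to the 80th percentile, which keeps the SD small.

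**If slopes differ.** Effect at zero = average effect − (slope difference × m/s), with the slope difference in residual SD per baseline SD. With ratio 8 and slope difference 0.1: 0.396 − 0.1 × 8 = −0.404. The sign reverses.

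**The case against.** The strongest reply is that section 2.2 lists model terms and does not say that the Product test decides. The same fit yields a least-squares-mean difference, which PROC MIXED evaluates by default at the mean of the covariate. That is the average effect, with practically no loss of power. Centring and the choice of contrast may also be set out in a full protocol or analysis plan that is not shown. This stands, and it means that a reader may not infer that the trial's primary test is a comparison at zero. The article leaves that open.

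A reader might also infer that the interaction term itself costs the power. It does not: with baseline centred, the model with the interaction matches the one without it. The loss comes from reading the uncentred Product term.

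Nor does the document support a general statement that most of the power is lost. It gives no baseline mean or SD and no log scale, the only stated unit is CFU/g, and many infants may lack the administered strains at V2, which would put zero inside the data. The 80% is itself a yardstick, since the trial has no planned power.

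Finally, the safety analysis as a whole is not disabled. The comparisons of the proportion of infants with an adverse event and of event counts in section 2.5 do not use this model.

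What survives is more than a missing detail. The article does state a model, and the term in it that carries the product's name gives the wrong quantity when read directly.

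**Conclusion.** The point holds in conditional form. The stated model, with its uncentred baseline, has a Product term that is the arm difference at a baseline of zero, and no other quantity is named as the result. That follows from the model alone and needs no assumption about the data.

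The size of the damage does need assumptions: that the Product main-effect test is the one read, and a value for the baseline mean/SD ratio. Under the first, an 80% test becomes about 71% at a ratio of 0.5, 51% at 1, 24% at 2 and 6% at 8. For the microbiota endpoints the loss can therefore be anything from negligible (very skewed raw counts, strains mostly absent at V2) to severe (log counts of commonly detected groups). For SIgA it depends on a ratio that is not given. For weight, length and head circumference, where zero is impossible and the spread is small against the mean, it is near total over any reasonable range.

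**What to change.** In section 2.2, make the primary model Y = Product + Baseline, and name the Product least-squares-mean difference with its 95% CI as the result for each endpoint. Equally good for power: keep the interaction, centre baseline at its overall mean, and name the difference at the mean baseline as the test. In either case, report Product × Baseline only as a supportive check, with baseline centred. Carry the same wording into sections 2.3 (SIgA) and 2.5 (growth).

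The cost is about one line of text, settled before unblinding. No extra data or infants are needed, and the information on whether the effect varies with baseline is kept.

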### Secondary analysis

2.3

The above-mentioned ANCOVA model will be conducted for analysis of the V2–V3 change in salivary SIgA levels.

A within-group analysis to compare V2 and V3 values (e.g., fecal microbiota and salivary SIgA) will be conducted in each product group using a paired Student's *t*-test or a Wilcoxon signed-rank test, depending on the condition of application of the statistical test.

The outcomes related to GI symptoms and well-being (weekly average number of stools, stool form, amount of stools, color of stools, number of crying incidents, and duration of crying) will be analyzed using the following ANOVA model for repeated measurements (subject will be considered as a random effect, using SAS PROC MIXED):

Y = Product + Week + (Product × Week)

where Y = study endpoint at Wr (D8 to D15), W1 (D16 to D22), W2 (D23 to D29), W3 (D30 to D36), or W4 (D37 to D43)

Product = study products

Week = W1 to W4 weeks (between V2 and V3 visits)

Product × Week = interaction between the product and the week

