### Study endpoint

3.12

The primary endpoints are the V2-V3 changes in composition of the fecal microbiota, including *Bifidobacterium bifidum*, *Bifidobacterium longum ssp. infantis*, *Lactobacillus helveticus*, *Clostridium perfringens*, *Enterococcus*, *Enterobacteria*, and *Bacteroides* (defined as V3 [D44]-V2 [D15]). The secondary endpoints are:♦the V2-V3 change in SIgA antibody levels in saliva samples♦GI symptoms and well-being, as recorded daily by parents in the infant diaries; the following outcomes will be calculated on a weekly basis:1.average daily number of stools; for each subject, the total number of stools per day will be recorded in a 7-day diary, and then the average daily number of stools will be calculated. (The same procedure will be applied for the following endpoints.)2.average daily Infant Stool Form scores consistency (4-point scale), average weekly amount (4-point scale, letters will be replaced by figures, i.e., “A” to “1,” “B” to “2,” etc.) and color (6 categories), using the validated scale for preterm and term infants proposed by Bekkali et al.^[22]^3.average daily number of crying episodes4.average daily duration of crying episodes.♦the changes in growth parameters such as weight, length, and head circumference♦the numbers of AEs and serious AEs

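### The role of the run-in week in the diary model is contradictory and it is not used as a baseline; stool colour is averaged without a stated score

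*Protocol article*

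**What the plan says.** The protocol article, Secondary analysis, specifies one repeated-measures model for the diary outcomes: "Y = Product + Week + (Product × Week"), with the note "subject will be considered as a random effect, using SAS PROC MIXED". Two definitions follow it:

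- The response is the "study endpoint at Wr (D8 to D15), W1 (D16 to D22"), followed by W2, W3 and W4, which ends on D43. That is five windows.
- The factor is "Week = W1 to W4 weeks (between V2 and V3 visits"). That is four levels, without Wr.

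The model has no baseline term. The outcomes it covers are "weekly average number of stools, stool form, amount of stools, color of stools, number of crying incidents, and duration of crying".

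Under Study endpoint, a numeric rule is given for stool amount (letters become figures). Colour is described only as "and color (6 categories), using the validated scale for preterm and term infants", with no order or score. The same section carries the averaging procedure for stool number over to the diary endpoints listed after it.

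Elsewhere, the Primary analysis adjusts for the V2 value, and the same ANCOVA is used for salivary SIgA and for growth. Under Study procedure and clinic schedule, the switch of formula is to be complete within D1 to D8, diaries run from D8, and the intervention starts at V2 (D15).

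**The concern.** A Wr record has a response but no level of Week, so the model cannot be fitted to the data it lists. Someone has to decide what Wr is, and the text points two ways. As a response, Wr brings a week before product use into the treatment comparison. If it is dropped, a baseline that every family is asked to record goes unused, although the protocol adjusts for baseline in its microbiota, SIgA and growth models.

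The choice affects both the size of the estimate and its standard error, and as written it could be made after the data are seen. The trial's hypothesis concerns digestive as well as immune function, and the diary carries the symptom side of digestive function.

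Colour is a separate matter. A mean over categories needs a number for each category, and the document gives none.

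**Working it through.** **No figure to reproduce.** The article states no effect size, SD, correlation or power for the diary outcomes, and says under Participant and eligibility that no formal sample size calculation was made. What follows is illustration, apart from the counts of windows and days.

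**Windows.** Wr covers D8 to D15: 15 − 8 + 1 = 8 days. W1 to W4 cover 7 days each, D16 to D43, which is 28 days and matches the 28 sachets supplied. D15 thus falls in Wr and is also the stated start of intervention.

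**Reading A: Wr as a fifth response week, Product main effect tested.** With effect δ in each of W1 to W4 and zero in Wr, the averaged effect is (0 + 4δ)/5 = 0.8δ. This needs a constant on-treatment effect but no assumption about correlation. A simulation of 200 trials (100 per arm, correlation 0.5, true effect 0.40 SD) gave a mean estimate of 0.320.

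**Reading B: Wr records drop out.** The effect stays at δ. Take weekly SD 1 and equal correlation r between any two weeks, which is what a random subject effect implies. Then, per infant:

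- unadjusted four-week mean: variance (1 + 3r)/4
- four-week mean adjusted for Wr: variance (1 + 3r)/4 − r²

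| r | Unadjusted | Adjusted for Wr | Ratio |
|---|---|---|---|
| 0.3 | 1.9/4 = 0.475 | 0.475 − 0.09 = 0.385 | 0.81 |
| 0.5 | 2.5/4 = 0.625 | 0.625 − 0.25 = 0.375 | 0.60 |
| 0.7 | 3.1/4 = 0.775 | 0.775 − 0.49 = 0.285 | 0.37 |

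**Power, for scale only.** Assume an effect of 0.4 SD, two-sided 0.05, and 50 infants per arm (the minimum the article cites; 100 are planned).

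| r | Reading A | Reading B | W1–W4 adjusted for Wr |
|---|---|---|---|
| 0.3 | 0.67 | 0.83 | 0.90 |
| 0.5 | 0.54 | 0.72 | 0.90 |
| 0.7 | 0.45 | 0.62 | 0.96 |

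With 100 per arm and r = 0.5 the three values are 0.83, 0.95 and 0.996.

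**If correlation fades with time.** Suppose the correlation is r between adjacent weeks and r^k between weeks k apart. The mean correlation of Wr with W1 to W4 is c = (r + r² + r³ + r⁴)/4. The variance of the four-week mean is v = [4 + 2(3r + 2r² + r³)]/16, and the ratio is 1 − c²/v.

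- r = 0.3: c = 0.106, v = 0.388, ratio 0.97
- r = 0.5: c = 0.234, v = 0.516, ratio 0.89
- r = 0.7: c = 0.443, v = 0.678, ratio 0.71

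The gain remains but is much smaller.

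**Colour.** Take two invented distributions over six categories: (0.4, 0.2, 0.1, 0.1, 0.1, 0.1) and (0.2, 0.2, 0.1, 0.1, 0.1, 0.3). The difference in mean score is 0.2 × (code of category 6 − code of category 1). Over the 720 ways of assigning 1 to 6, it runs from −1.0 to +1.0 and is negative in half. For a second pair, (0.30, 0.10, 0.10, 0.10, 0.10, 0.30) and (0.05, 0.20, 0.25, 0.25, 0.20, 0.05), coding in the listed order gives −0.25 × 7 + 0.10 × 7 + 0.15 × 7 = 0, while other codings reach ±1.6. Two clearly different distributions can therefore show no difference in means.

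**The case against.** A reader might infer that the planned treatment effects are diluted. The text does not establish that. Taken literally, Wr has no Week level, so its records would drop out and nothing is diluted. Dilution needs two choices the article does not state: a fifth level of Week, and the Product main effect as the test. With five levels, the Product × Week contrasts against Wr would use it as an implicit baseline and would not be diluted. That objection stands. However, no such contrast is named. Change from Wr, with variance (1 + 3r)/4 + 1 − 2r, is also less precise than covariate adjustment: 0.875 against 0.385 at r = 0.3, and 0.375 against 0.285 at r = 0.7.

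A reader might also take the missing covariate for a flaw in validity. It is not one. Randomisation protects the unadjusted comparison, and an unadjusted repeated-measures model is a legitimate choice for secondary endpoints. That it differs from the primary ANCOVA is not in itself a contradiction.

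The precision figures rest on assumed correlations. Infants of this age change quickly and the formula switch ends just before Wr, so fading correlation is plausible and the equal-correlation ratios may be optimistic.

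Finally, a reader might call the colour result meaningless because colour is nominal. The document says only that there are six categories from a cited scale, which is not available here. If that scale is ordered, a mean score is crude but interpretable. What stands is that colour is in the list for a linear model with neither order nor score given.

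None of this removes the conflict between the two definitions. The article prints the model with its terms defined, so this is not detail left to an analysis plan.

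**Conclusion.** The point holds as an inconsistent specification plus a missed gain in precision. It does not show that the planned analysis is biased.

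- **Certain from the text:** Wr is in the response and not in Week; there is no baseline term; six-category colour goes into the linear model with no score; D15 lies in Wr and is also the start of intervention.
- **Conditional:** shrinkage to 4/5 applies only under Reading A with a constant effect. Loss of precision applies only under Reading B. They are alternatives and do not add up.
- **Illustrative:** adjusted variance is 0.81, 0.60 and 0.37 of unadjusted under equal correlation of 0.3, 0.5 and 0.7, or 0.97, 0.89 and 0.71 if correlation fades geometrically.

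The colour problem affects one of six diary outcomes. All six are secondary; the primary microbiota analysis uses another model and is untouched. The change should be made, but the trial's main conclusion does not depend on it.

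**What to change.** 1. Define the response at W1 to W4 only and add the run-in value: Y = Product + Week + Product × Week + Wr, with subject as a random effect as now.
2. Name the Product difference averaged over W1 to W4 as the test.
3. Reconcile D15: state whether that day's diary entry belongs to the pre-product window, given that Wr includes it and the schedule starts the intervention on it.
4. Take colour out of the linear model. Analyse the proportion of stools or days in each category with a categorical model, for example a logistic GEE.

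Cost: a wording change made before unblinding. Diaries already start on D8, so no new data are needed. The one downside is that infants without run-in diary entries need a simple, pre-stated rule for a missing baseline.
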